### Study population

#### **
*Inclusion criteria*
**

All consecutive critically ill patients admitted to the ICU aged ≥18 years at the time of ICU admission and with an expected length of ICU stay of over one day will be included as informed consent is obtained.

Data from patients that are included in the study, but who do not receive any study drug and are discharged from the ICU within 24 h will be discarded from further analysis. Patients who received at least one dose will remain in the study and patients in whom study medication had to be halved or stopped, e.g., because of prolonged QTc time or other side effects, will remain allocated to their study group and analyzed on an intention-to-treat basis.

#### **
*Exclusion criteria*
**

The following will be considered exclusion criteria: no informed consent obtained; history of epilepsy, Parkinson’s disease, hypokinetic rigid syndrome, dementia or alcohol withdrawal syndrome; patients admitted to the ICU for any other neurological disease (including post-cardio-pulmonary resuscitation patients, and patients admitted with coma due to overdose); patients treated with anti-psychotic therapy over the last 30 days prior to ICU admission; prolonged QTc-time (>500 msec) or history of clinically relevant ventricular arrhythmia in last 12 months; pregnancy/breast feeding; documented delirium prior to ICU admission; reasons that impair delirium assessment with the CAM-ICU (serious auditory or visual disorders, unable to understand Dutch or English; severely mentally disabled; serious receptive aphasia); ICU-stay less than one day; moribund and not expected to survive two days; known allergy to haloperidol.

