### Safety monitoring and safety issues

A Data Safety Monitor Board (DSMB) is established for this study to perform ongoing safety surveillance and to perform interim analyses on the safety data. This is an independent committee composed of two physicians/researchers (a psychiatrist and an anesthetist) and a statistician. The DSMB will perform all interim analyses. To assess side effects of haloperidol and to determine superiority of the intervention or placebo the DSMB will be unblinded for this study, while all researchers remain blinded. Furthermore, the study will be monitored by an independent researcher who will monitor the trial master file, and perform random checks of informed consent forms, drug accountability lists, and source data of primary and secondary outcome measures.

Concerning safety issues, during a patient’s treatment with the study medication, known side effects of haloperidol [34] are pro-actively collected with a special focus on prolonged QTc-time, drowsiness, extrapyramidal symptoms, and agitation and sedation effects. All side effects will be collected during patients’ treatment with the study medication until 24 h after stopping the study medication. In case of the occurrence of side effects, physicians can reduce the dosage or stop the study medication, depending on the severity of the occurred side effect and at the discretion of the attending physician. Only for prolonged QTc-time, strict stopping rules are applied, as described below. To detect side effects of haloperidol, the protocol dictates that patients are physically examined every day for known signs of extrapyramidal symptoms (signs of Parkinsonism and/or akathisia and/or dystonia). Furthermore, daily QTc-time is calculated using a 12-lead ECG or a monitor lead ECG. A QTc-time of over 500 msec combined with an increase of over 10% of baseline QTc-time is defined as prolonged QTc-time. In case of QTc-time prolongation, the study drug is temporarily stopped until QTc-time is normalized. After normalization of QTc-time (<500 msec) the study drug will be restarted. If QTc-time becomes prolonged again, the study drug will be stopped definitively. The patient will remain allocated to the original study group.

To determine long-term side effects, such as rigidity, and quality of life, a recommended and validated quality of life questionnaire, SF-12 [35], is taken at the time of admission and is sent to the patients 1 and 6 months after ICU admission.

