The following adverse events will be collected: serious adverse events; non-serious adverse events that are considered by the investigator to be possibly related to the study drug (e.g., prolonged QTc-time, drowsiness, extrapyramidal symptoms, agitation and sedation effects); adverse events that lead to permanent discontinuation of the study drug administration. A serious adverse event is any untoward medical occurrence or effect at any dose that results in one of the following outcomes and is not classified as a clinical outcome of delirium or the underlying disease using the description: death that is not related to the underlying disease or sequel of the underlying disease, or death that is considered by the investigator to be related to the study drug; prolonged inpatient hospitalization or re-hospitalization; a life-threatening experience (that is, immediate risk of dying); persistent or significant disability/incapacity; considered significant by the investigator for any other reason.

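### The mandatory QTc stop needs both a value above 500 msec and a rise of more than 10%, so eligible patients with a baseline of about 455–500 msec can stay on study drug above the protocol's own 500 msec limit, subject only to physician discretion

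*Protocol article*

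**What the plan says.** The protocol article uses QTc limits in three places.

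- **Entry** (Study population, Exclusion criteria). Patients are excluded for "prolonged QTc-time (>500 msec) or history of clinically relevant ventricular arrhythmia in last 12 months". The limit is absolute, so a baseline of 500 msec or less is eligible.
- **Mandatory stop** (Safety monitoring and safety issues). "A QTc-time of over 500 msec combined with an increase of over 10% of baseline QTc-time is defined as prolonged QTc-time". Meeting this definition triggers a temporary stop, and a second episode ends treatment: "If QTc-time becomes prolonged again, the study drug will be stopped definitively".
- **Restart** (same section). "After normalization of QTc-time (<500 msec) the study drug will be restarted". This limit is again absolute and makes no reference to baseline.

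The same section singles QTc out among the side effects: "Only for prolonged QTc-time, strict stopping rules are applied, as described below". For side effects in general, "physicians can reduce the dosage or stop the study medication, depending on the severity of the occurred side effect", at the attending physician's discretion. Monitoring is frequent: "daily QTc-time is calculated using a 12-lead ECG or a monitor lead ECG".

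**The concern.** The term prolonged QTc-time has two meanings in one article: above 500 msec at entry, and above 500 msec plus a rise of more than 10% on treatment. Because the second meaning governs the mandatory stop, the rule is loosest for the eligible patients who start closest to the exclusion limit. They can have a QTc that would have kept them out of the trial, and that would not let them resume after a pause, yet nothing obliges anyone to pause the drug.

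What is at stake is individual patient safety. The drug is given as prophylaxis, and the Background section promises extra attention to side effects for that reason. That section describes ventricular arrhythmias as extremely rare but dose dependent. The ICU precedent it cites used 3x1 mg a day, and this trial adds an arm at 3x2 mg. QTc is the one side effect for which the protocol says it applies a strict rule, and in this range the strict rule does not operate.

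**Working it through.** The article gives no figure of its own to reproduce. The check is direct arithmetic on the stated limits, taking baseline to be the QTc at entry.

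**Inputs**
- Largest eligible baseline: 500 msec (Exclusion criteria).
- Stop condition: QTc > 500 msec and QTc > 1.10 × baseline (Safety monitoring and safety issues). The wording joins the two conditions, and nothing in the text supports reading them as alternatives.
- Restart limit: < 500 msec (same section).
- Dosing: three times a day (Intervention and control group).

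**Step 1: mandatory threshold.** Both conditions must hold, so the stop applies above max(500, 1.10 × baseline).

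**Step 2: where the gap opens.** 1.10 × baseline = 500 gives baseline = 500/1.10 = 454.5 msec. At or below this value, any QTc above 500 is already a rise of more than 10%, and the two-part rule is the same as an absolute limit.

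**Step 3: size of the gap above 454.5 msec.**

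| Baseline (msec) | 1.10 × baseline = mandatory stop above | Range above 500 with no mandatory stop |
|---|---|---|
| 460 | 506 | 6 |
| 470 | 517 | 17 |
| 480 | 528 | 28 |
| 490 | 539 | 39 |
| 500 | 550 | 50 |

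**Step 4: the same reading in two patients.** At an on-study QTc of 520 msec:
- baseline 460: 520/460 = 1.130, a 13.0% rise, so the drug must be stopped;
- baseline 480: 520/480 = 1.083, an 8.3% rise, so no stop is required.

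In general, a given on-study QTc forces a stop only at baselines below QTc/1.10. That is 472.7 msec for a QTc of 520, 481.8 for 530 and 490.9 for 540.

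**Step 5: comparison with restart.** With a baseline of 480, a reading of 510 is a 6.25% rise (510/480 = 1.0625), and dosing may continue. A patient already paused could not resume at 510, because restart requires a value below 500.

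**Step 6: effect of an absolute hold.** With a temporary hold at any QTc above 500, the threshold is 500 msec at every baseline and the gap is zero.

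**The case against.** The strongest reply is that this is an openly stated design choice that can be followed as written. Entry and on-treatment limits do different jobs: one screens out patients at high risk, the other asks whether QTc has risen on the drug. A rise from 460 to 520 and a rise from 480 to 520 are different signals, and a relative criterion is meant to separate them. QTc may be read from a 12-lead ECG or a monitor strip, so some difference between readings is to be expected. For a patient with a baseline of 495, a bare 500 msec limit would act on a change of 6 msec. A restart level below the stop level is also ordinary practice and avoids repeated stopping and starting.

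Much of this stands. The 10% condition may well be deliberate, although the article gives no reason for it, and the difference between stop and restart levels is not a fault in itself. But variation around a high baseline argues against ending treatment permanently. It argues less strongly against a short hold.

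Three stronger readings are tempting, and the documents support none of them.

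- *Patients in the gap are unprotected.* They are not. QTc is calculated daily, the physician may reduce or stop the drug, and the DSMB carries out ongoing safety surveillance. The collected events include "non-serious adverse events that are considered by the investigator to be possibly related to the study drug (e.g., prolonged QTc-time". The Study population section also foresees halving or stopping the drug for a prolonged QTc. None of this is a mandatory pause in the range at issue, and that pause is all that is absent.
- *Continuation up to 550 msec is typical.* That figure needs a baseline of exactly 500 msec. At 460 the gap is 6 msec.
- *Repeated readings above 500 msec should end treatment whatever the rise.* Nothing in the documents supports such a rule, and it would permanently remove patients near the limit, including those on placebo, because of measurement variation.

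**Conclusion.** The point holds as a patient-safety improvement that should be made. It is not an error in the analysis or a rule that cannot be followed. For eligible baselines above 454.5 and up to 500 msec, the mandatory stop begins somewhere between just over 500 and 550 msec, above the limit the protocol itself uses for entry and for normalization. In that range only the physician's judgement applies.

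This rests on two readings: that the stop condition requires both parts, and that baseline means the entry QTc. The article gives neither a baseline nor an on-study QTc distribution, so the number of patients affected cannot be estimated, and no harm is shown.

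A reader might infer that the primary result is compromised. It is not: the rule is the same in all three arms, and the 28-day survival analysis, the sample size and the alpha are unaffected.

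**What to change.** In Safety monitoring and safety issues:

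1. Hold study drug temporarily at any on-study QTc above 500 msec, whatever the percentage rise, and resume below 500 msec as already stated.
2. Keep the definitive stop as it is now: a second episode above 500 msec with a rise of more than 10% from baseline. A hold without that rise does not count towards it.
3. Tabulate any on-study QTc above 500 msec by arm, so that values in the present gap are visible whether or not they meet the two-part definition.

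No new measurement is needed, because QTc is already calculated daily. The cost is some extra temporary pauses and slightly less exposure in patients with a high baseline, in every arm including placebo. With three doses a day and one QTc a day, a pause costs at least about 1 × 3 = 3 doses. It costs more if the next value is not below 500, and a patient whose baseline is at or near 500 could wait longer. The article reports that the protocol had already passed the ethics committee, so the new wording would be a change to an approved document.

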## Background

Delirium is a neuropsychiatric disorder characterized by an acute onset of confusion, inattention, and a change in level of consciousness that tends to fluctuate during the day [1,2]. The incidence of delirium in intensive care unit (ICU) patients is high [3-6], approximately 30–50%. Further, its occurrence is associated with detrimental outcome, including prolonged duration of mechanical ventilation, increased ICU and hospital length of stay (LOS) [4-6], unplanned removal of tubes and catheters [6], increased mortality [6-8], and long-term cognitive disturbances [9,10]. Therefore, a strategy that can prevent delirium in high-risk patients may also decrease short-term (i.e., 28-day) mortality.

The first step in the management of delirium is to treat the underlying disease. If delirium does not subside, haloperidol is the most frequently used pharmacologic treatment of delirium. However, this drug may also be used to prevent delirium. In non-ICU patients, beneficial effects have been reported of prophylactic haloperidol in older and surgical patients [11,12]. For critically ill patients, data concerning prevention with anti-psychotic drugs are scarce and inconsistent [13-15]. In one retrospective cohort study, ICU patients who received haloperidol were found to have a lower mortality rate compared to ICU patients that did not receive haloperidol [16]. Only one prospective, randomized trial in critically ill patients is available, showing that haloperidol prophylaxis in non-cardiac surgical ICU patients had beneficial effects on delirium incidence and the number of delirium free-days [17]. However, only a very low dose, for 12 h infusion of haloperidol was administered and many of the patients were in the ICU for less than 24 h [17]. Thus, there are no large, definitive trials that have studied the effect of haloperidol prophylaxis in ICU patients.

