Recently, a model was developed and validated to predict delirium in ICU patients [18]. With this model, the effectiveness of preventive strategies can be compared in different groups that differ in *a priori* risk of delirium. This delirium prediction model was used to identify high-risk ICU patients (i.e., *a priori* risk of delirium >50%). Compared to a historical control group, prophylactic low-dose haloperidol was associated with better delirium related outcomes. In this high-risk group (>50%) of critically ill patients, incidence of delirium was significantly lower in the preventive treatment group (65%), compared to the control group (75%). Furthermore, haloperidol prophylaxis was associated with a hazard rate of 0.8 for 28-day mortality [19]. However, because of the pre-/post-implementation design of this trial, other factors that may have changed between the study periods may have influenced these findings. Nevertheless, the results suggest that prevention of delirium might be beneficial in critically ill patients. Since no relevant side effects associated with the administration of a low dosage of haloperidol were reported in the prophylactic studies [11,12,17,19], it is conceivable that a higher dose of haloperidol may exert more pronounced beneficial effects. Furthermore, the optimal dosage of haloperidol in critically ill patients, as well as the occupancy levels of dopamine-2 receptors and sigma-1 receptors when administering haloperidol, remain unknown. Therefore, in the present study proposal the effects of two dosages of haloperidol versus placebo will be determined.

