Given the fact that the development of delirium can be predicted only 24 h after ICU admission, and the clear relation between time to treatment with haloperidol and the duration of delirium [19], initiation of prophylaxis as early as possible is warranted. Based on our historical data, the median predicted risk of delirium is approximately 35% in patients with an expected stay on the ICU of over one day; this is considered a high risk for delirium development. A clinical estimation of an ICU LOS >1 day is possible within the first few hours after ICU admission. Previous studies that included patients using similar criterion of an expected ICU LOS were found feasible [20,21]. Therefore, the clinical estimation by the attending ICU-physician of an ICU LOS >1 day will be used as an inclusion criterion for this study, in which the prediction to develop delirium (using the PRE-DELIRIC model [18]) will be used to facilitate post-hoc analyses to investigate which patients benefit most from prophylactic therapy. By using the PRE-DELIRIC score as an *a priori* determined post-hoc analysis, we will learn if the putative beneficial effect of haloperidol is related to the risk to develop delirium, or comparable in all patients, independent of the baseline risk to develop delirium. In addition, it will facilitate the determination of a cut-off level for the PRE-DELIRIC score.

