### Objectives

Definitions of variables in objectives are reported in Table 1.

**Table 1 T1:** Definition of study objectives

**Objective**	**Definition**
*Survival days in 28 days*	Number of days that patients survive in 28 days. All patients will be classified as either ‘alive at study day 28’ or, if dead, ‘dead at study day 28’ on an intention-to-treat basis.
*Delirium diagnosis*	Patients are diagnosed as delirious when they have at least one positive CAM-ICU screening during their complete ICU stay. Patients who were not delirious during their ICU-stay are considered as non-delirious patients.
*Delirium-and-coma-free days in 28 days*	Number of days that the patient is alive and not delirious and not in coma over 28 days starting from the day of inclusion. A delirium-and-coma-free day is defined as a negative CAM-ICU screening with a Richmond Agitation Sedation Score (RASS) greater than (more alert than) -3/-4/-5 during a day. In case a delirious patient is discharged to the ward, a delirium-free day is defined as a delirium observation scale score [30] of less than 3 during a complete day.
*Duration of mechanical ventilation*	Time in days that the patient is on the mechanical ventilator. If the patient is ventilated mechanically several times during one ICU admission, then the ventilator times are added. Both invasive and non-invasive ventilation will be registered. Ventilator-free days (in 28 days) will be calculated.
*Incidence of re-intubation*	Patients who need to be intubated within 28 days from randomization, following a previous extubation, irrespective of the reason for re-intubation, are counted as incident case for re-intubation.
*Incidence of ICU readmission*	Patients who need to be readmitted to the ICU during within 28 days from randomization, irrespective of the reason for readmission, are counted as incident cases for ICU readmission.
*Side effects*	Drowsiness, agitation, QTc-time prolongation (using 12-leads ECG or monitor strip with Bazett’s formula) and development of extra pyramidal symptoms such as tandem gait, dystonia, tremor, myoclonus, tics, rigidity, akathisia [31], determined daily by physical examination by the intensivist.
*Serious adverse event*	Any untoward medical occurrence or effect at any dose that results in one of the following outcomes and is not classified as a clinical outcome of delirium or the underlying disease using the description above:

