	- death that is not related to the underlying disease or sequel of the underlying disease, or death that is considered by the investigator to be related to study drug
	- prolonged inpatient hospitalization or re-hospitalization
	- a life-threatening experience (that is, immediate risk of dying)
	- persistent or significant disability/incapacity
	- congenital anomaly/birth defect
	- considered significant by the investigator for any other reason
*Sudden unexpected serious adverse reactions*	Unexpected adverse reactions are adverse reactions, of which the nature, or severity, is not consistent with the applicable product information. Adverse reactions are all untoward and unintended responses to an investigational product related to any dose administered.

#### **
*Primary objective*
**

To determine the effect of prophylactic haloperidol use on 28-days survival.

#### **
*Secondary objectives*
**

There are seven secondary objectives:

1. To determine the effect of prophylactic haloperidol use on 90-day survival; survival analysis stratifying for delirium incidence will be performed.

2. To determine the effect of prophylactic haloperidol use on the incidence of delirium.

3. To determine the effect of prophylactic haloperidol use on the number of delirium- and coma-free days in a period of 28 days.

4. To determine the effect of prophylactic haloperidol use on delirium related outcomes: time to successful extubation, incidence of re-intubation, incidence of ICU readmission, and incidence of unplanned removal of tubes and catheters.

5. To evaluate the incidence and severity of side effects of haloperidol prophylaxis.

6. To determine the effect of preventive haloperidol use on quality of life 1 and 6 months following ICU admission compared with a baseline measurement at ICU admission using the Short Form-12 (SF-12) questionnaire.

7. *A priori* defined post-hoc analyses:

a. To determine the preventive effectiveness of haloperidol in different patient groups based on the *a priori* risk to develop delirium: patients with a predicted risk up to 50%, 50–70%, 70–90%, above 90% will be evaluated.

a. To determine the preventive effectiveness of haloperidol in different patient groups: medical/surgical/trauma patients, per acute physiology and chronic health evaluation-II (APACHE-II) score (<20, 20–25, >25)

a. Effectiveness of prophylaxis when delirium is diagnosed based on 1, 2, or more days with positive CAM-ICU scoring.

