**Figure 1 F1:**
[figure not shown]
CONSORT flowchart of patient enrollment.

A safety, futility, and superiority interim analysis will be performed by the DSMB after 175, 350, 500 (safety and futility) and 1,000 (safety and superiority) patients are included. Differences in serious adverse events between intervention and placebo are used for safety analyses and the primary endpoint 28-day survival is used to determine futility or superiority of intervention or placebo.

After the inclusion of 1,000 patients, superiority will be tested. A proven superiority (*P < 0.003, two-sided)* of any dose of haloperidol over placebo or a proven superiority (*P < 0.003, two-sided)* of placebo over haloperidol determined during the interim analysis will result in an alpha of 0.049 (two-sided) for the final analysis. This alpha distribution was calculated by an independent statistician according to the method of Lan-DeMets cumulative alpha spending function of O’Brien-Fleming alpha spending [36].

Data will be analyzed according to the intention-to-treat principle. For the descriptive statistics, continuous variables will be given as mean with standard deviation or median and inter quartile ranges, depending on their distribution. Normally distributed variables will be tested using Student’s *t*-test for comparison and Mann-Whitney U-tests for non-normally distributed variables. Categorical (and binary) variables will be presented as numbers and percentages and will be analyzed using the χ^2^ test. Survival analyses with Kaplan-Meier curves will be used as graphical representation. Cox proportional hazard regression analyses will be used to estimate the hazard ratio for survival with the use of haloperidol versus placebo. Furthermore, we will perform adjusted analyses for relevant covariates (including delirium, APACHE-II score, age, sex, sepsis, and other differences between the three study groups irrespective of the possible imbalance between the three groups). For this covariate analysis, univariate logistic regression analysis will be performed first in order to test the strength of the relationship. Subsequently, variables significantly associated with the dependent variable will be included in the covariate analyses.

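### Serious events attributed to delirium are exempt from the SAE count and nowhere shown by arm, so the SAE comparison omits harm or benefit that acts through delirium

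*Protocol article*

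**What the plan says.** The SAE definition appears twice in the protocol article, in Table 1 (Objectives) and in Safety monitoring and safety issues. Each time an event must lead to one of the listed serious outcomes, among them prolonged hospitalisation or re-hospitalisation, immediate risk of dying, and lasting disability. Each time it is left out if it is judged an outcome of delirium or of the underlying disease. In the safety section the event counts only if it "is not classified as a clinical outcome of delirium or the underlying disease"; Table 1 words the condition as "is not classified as a clinical outcome of delirium or the underlying disease using the description above".

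The interim paragraph of Sample size calculation and statistics gives the use of the count: "Differences in serious adverse events between intervention and placebo are used for safety analyses". Safety is part of every look, "after 175, 350, 500 (safety and futility) and 1,000 (safety and superiority) patients are included".

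Delirium is also a target of the drug. The second secondary objective reads "To determine the effect of prophylactic haloperidol use on the incidence of delirium".

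**The concern.** Whether an event enters the safety count depends partly on its attribution to delirium. Delirium occurs after randomisation, and its frequency is expected to differ between arms. Three consequences follow.

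- Serious harm or benefit that acts through delirium is absent from the SAE comparison, whichever way it runs.
- If investigators attribute more events to delirium than delirium causes, and haloperidol prevents delirium, more events are removed on placebo and haloperidol can show an excess that is not real.
- The Background lists drowsiness and agitation as side effects of haloperidol. The Delirium treatment section defines delirium by a positive CAM-ICU and recognises a hypoactive form. If a drug effect is read as delirium, its serious consequences can leave the count.

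At stake is how the DSMB and the final report read the one between-arm measure that the article names for the safety analyses.

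**Working it through.** The article gives no SAE rate, so there is no figure to reproduce. What follows is an illustration with labelled assumptions.

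**Inputs**
- Delirium incidence p: 75% control and 65% haloperidol, from the earlier high-risk study in the Background. That study had a pre-/post-implementation design and enrolled patients with predicted risk above 50%.
- Alternative p: 35% on placebo, because "the median predicted risk of delirium is approximately 35% in patients with an expected stay on the ICU of over one day", and 25% on haloperidol (assumed).
- Serious-event risk in patients with delirium (rd) and without (rn): assumed.
- Share f of delirious patients' serious events that is exempted: assumed, 0 to 1.
- About 333 per arm at the 1,000-patient look (1,000/3, equal allocation assumed).

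**Formulas**
- All serious events: T = p·rd + (1 − p)·rn
- Counted as SAE: C = p·rd·(1 − f) + (1 − p)·rn
- Counted difference, haloperidol minus placebo: (p_placebo − p_haloperidol)·[rn − rd·(1 − f)]

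With less delirium on haloperidol, this difference is positive only if f > 1 − rn/rd. If the extra risk in delirious patients is caused by delirium, 1 − rn/rd is the share of their events that delirium causes. At exactly that share, C = rn in both arms.

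**Delirium 75% vs 65%, rd = 30%, rn = 15%** (threshold 1 − 15/30 = 0.5)

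| f | Placebo | Haloperidol | Difference (points) |
|---|---|---|---|
| 0 (all events) | 26.25% | 24.75% | −1.5 |
| 0.25 | 20.6% | 19.9% | −0.75 |
| 0.5 (accurate) | 15.0% | 15.0% | 0 |
| 0.75 | 9.4% | 10.1% | +0.75 |
| 1 | 3.75% | 5.25% | +1.5 |

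For example, at f = 0.75 on placebo: 0.75 × 0.30 × 0.25 + 0.25 × 0.15 = 0.05625 + 0.0375 = 9.4%.

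**Delirium 35% vs 25%, same risks.** The differences in points are the same. At f = 0.75 the rates are 12.4% vs 13.1% (ratio 1.06), and at f = 1 they are 9.75% vs 11.25% (ratio 1.15).

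**Equal risk, rd = rn = 20%, delirium 75% vs 65%.** The threshold is 0: delirium causes none of these events, so any exemption is over-attribution. Counted rates are 16.25% vs 16.75% at f = 0.25 and 5.0% vs 7.0% at f = 1. The false excess is 0.5 to 2.0 points, with ratios from 1.03 to 1.40.

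**Size at 1,000 patients.** A false excess of 0.5 to 2.0 points is 333 × 0.005 = 1.7 to 333 × 0.02 = 6.7 patients per arm. For 5.0% vs 7.0%, the standard error is √(2 × 0.06 × 0.94/333) = 0.0184, so the chance of nominal significance in that direction is Φ(0.02/0.0184 − 1.96) = 19%. Across the false-excess settings above, the chance is about 4% to 19%, against 2.5% with no shift.

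**Hidden harm.** If the drug adds h points of serious events and a share g of them is classed as delirium, h·(1 − g) remains visible. With assumed h = 3 and g = 0.5, 1.5 points are seen.

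**The case against.** The strongest reply is that the rule exempts events attributed to delirium, not every event in a delirious patient. An arrhythmia in a delirious patient that is not put down to delirium still counts. Investigators are blinded. With accurate attribution the count is neutral, as the row f = 0.5 shows. This stands. A reader might infer that an effective dose will look harmful, or take ratios such as 1.15 or 1.40 as expected values. The article does not support that: those ratios need every event in delirious patients to be exempted, and no passage says so.

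The second reply is that much of what is exempted is compared elsewhere. Delirium incidence, delirium- and coma-free days, ventilation, re-intubation, ICU readmission and tube or catheter removal are outcomes, and 28-day survival is examined at the interims. A drug that produced positive CAM-ICU screens would raise delirium incidence. Named side effects are actively collected, adverse events leading to permanent discontinuation are recorded, and the unblinded DSMB carries out ongoing safety surveillance. Keeping disease outcomes out of the SAE count is acceptable where they are compared by arm in another table. All this stands and limits the point.

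Two gaps remain. Prolonged hospitalisation, life-threatening events and disability attributed to delirium have no stated between-arm comparison; the SF-12 touches disability only indirectly. And side-effect collection ends 24 hours after study drug stops, while delirium itself stops study drug, so that safeguard closes soon after delirium begins.

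The fuller list of delirium outcomes may be in the full protocol. Its absence from the article is not criticised here.

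**Conclusion.** The point holds in a limited form. As written, the between-arm SAE comparison omits serious harm or benefit that acts through delirium, and the article provides no tabulation of the omitted events by arm. This much does not depend on attribution error.

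A false excess on haloperidol depends on two assumptions: that haloperidol lowers delirium incidence, and that the exempt share exceeds 1 − rn/rd. In the illustrations it is 0.5 to 2.0 points and would seldom reach nominal significance. Hidden harm depends on drug effects being read as delirium. The article gives neither the event risks nor the exempt share, so the likely direction cannot be determined. The expected distortion is modest. This is a cheap improvement to the safety reporting; it does not show that the safety monitoring would fail.

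**What to change.** Keep the SAE definition if it is wanted for reporting purposes. Record every event that meets a seriousness criterion but is exempted as a delirium outcome. For each DSMB look and for the final report, tabulate these events by arm beside the SAE table, with a combined total irrespective of attribution. The combined total corresponds to f = 0 above and follows the all-event difference; the separate column shows how much depends on attribution.

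The cost is a wording change and somewhat more event entries in an ICU population where serious events are common. Several of the related outcomes are already collected. Treatment, design and sample size are unaffected.
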